## Abstract

**Introduction:**

Colorectal cancer is the fourth most common cancer in the UK and an important cause of cancer-related death. In 20% of patients, there is metastasis to the liver or beyond at the time of diagnosis. The management of synchronous disease is complex. Conventional surgery removes the colorectal primary first, followed by chemotherapy, with resection of liver metastases as a final step. Advances in the availability and safety of liver surgery, anaesthesia and critical care have made two alternative options feasible. The first is synchronous resection of the primary and liver metastases. The second is resection of the metastatic disease as the first step, termed the reverse or liver-first approach. Currently, evidence is inadequate to inform the selection of care pathway for patients with colorectal cancer and synchronous liver-limited metastases. Specifically, optimal pathways are not defined and there is a dearth of prospectively recorded cohort-defining factors influencing treatment selection or outcome.

**Methods and analysis:**

Colorectal cancer with Synchronous liver-limited Metastases: an Inception Cohort (CoSMIC) is an inception cohort study of patients with a new diagnosis of colorectal cancer with synchronous liver-limited metastases. The sequence of treatment received, and factors influencing treatment decisions, will be evaluated against European Society of Medical Oncology guidelines. Clinical data will be collected, and quality of life, morbidity, mortality and long-term outcome compared for different treatment sequences adjusted for prognostic factors. Disease-free survival or progression will be measured at 1, 2 and 5 years. A nested qualitative study will ascertain patient experiences and clinician perspectives on delivery of care.

**Ethics and dissemination:**

The full study protocol was independently peer reviewed by [name] [name] (University of Maastricht, Holland). CoSMIC has ethical approval from the National Health Service Research Ethics Committee (14/NW/1397). Results will be disseminated to healthcare professionals and patient groups, and may be used to design a definitive trial addressing areas of equipoise in treatment pathways, as well as optimising current pathways to improve outcomes and experiences.

**Trial registration number:**

NCT02456285, pre-results.

Strengths and limitations of this studyThis is the first prospective study directly comparing outcomes between the different surgical sequences of patients with colorectal cancer and liver-limited metastases.Completion of the C*o*lorectal cancer with Synchronous liver-limited Metastases: the protocol of an Inception Cohort (CoSMIC) study protocol will provide important new evidence about the treatment of patients with colorectal cancer with synchronous liver-limited metastases and provide objective evidence to guide future studies (including randomised evaluations) in this area.The variables involved in the treatment allocation of such patients are vast and currently do not allow for a randomised controlled trial. The current CoSMIC study is therefore limited to an observational, inception cohort study.

## Background

Bowel cancer is the fourth most common cancer in the UK.^1^ In Europe, colorectal cancer was the third most common cause of cancer and of cancer-related deaths in 2012.^2^ The liver is the most frequent site of metastasis in colorectal cancer: 14%–20% of patients have hepatic metastases at presentation and up to a further third will subsequently develop liver lesions.^3 4^ Liver metastases in patients with colorectal cancer are categorised as stage IV disease in which overall 5-year survival is 6%.^5^ However, stage IV bowel cancer encompasses a wide clinical spectrum of disease ranging from patients with isolated hepatic metastases to patients with widespread metastatic disease. Patients with surgically resectable lesions confined to the liver have reported 5-year survival rates of 25%–40%.^6^ Such patients represent a selected but important subgroup in whom long-term survival of approximately 17% at 10 years is feasible when the hepatic metastatic burden is removed.^7^

Patients who present with metastatic liver disease at a time point remote from their presentation with primary bowel cancer (termed metachronous disease) receive care focused on their new metastatic burden.^8 9^ In contrast, the management of patients who present with colorectal cancer and concurrent liver metastases (termed synchronous metastases) are more complex.^9 10^ These patients may have less favourable cancer biology and thus may be less likely to become long-term survivors.^11^ Logically, the management of patients with colorectal cancer with synchronous metastases can be dichotomised into those with hepatic disease together with extrahepatic metastatic disease and those with liver-limited metastatic disease. In the first category, systemic chemotherapy is the mainstay of treatment advocated in current guidelines for patients with advanced multisite metastatic disease of colorectal cancer origin.^9 12^

The second category of patients with liver-limited synchronous metastases represents a common and increasingly complex clinical management problem.^13^ Traditional management (referred to variously as the classical or staged approach) comprised resection of the colorectal primary tumour followed by adjuvant chemotherapy with liver resection being undertaken (if at all) as a subsequent operation.^13–15^ Key advances in the availability and safety of liver surgery, anaesthesia and critical care have made two alternative options feasible for patients with synchronous disease. The first is synchronous resection of the liver metastases and the colorectal primary.^13 15^ This has the attraction of removing the macroscopic tumour burden with a single operation. However, the morbidity of complex liver resection combined with major bowel resection may be considerable and there is some evidence of a negative effect on progression-free survival.^16^ The second option is resection of the liver metastatic disease as the first step, termed the reverse or liver-first approach.^17 18^ Liver-first surgery may be particularly applicable to patients with rectal cancer with synchronous liver metastases where preoperative long-course chemoradiotherapy for the rectal primary prior to surgical resection creates a potential ‘window’ in which liver resection may be undertaken.^19 20^ The liver-first strategy may also be oncologically advantageous by addressing the hepatic metastatic burden before progression in the liver renders this unresectable.^21^ A further potentially important benefit of the liver-first approach is that pelvic surgery may be either avoided or less extensive in patients with rectal tumours with a complete endoscopic, radiological and clinical response to chemoradiotherapy.^22^

Currently, evidence is inadequate to inform the selection of care pathway for patients with colorectal cancer with synchronous liver-limited hepatic metastases. Specifically, there is a dearth of prospectively recorded cohort-defining factors influencing treatment selection or outcome. European Society of Medical Oncology (ESMO) guidelines^9^ provide only a framework for the management of these patients. In the UK’s National Health Service (NHS), treatment decisions are made at multidisciplinary cancer team (MDT) meetings that include liver surgeons, colorectal surgeons, oncologists and specialist nurses. Factors considered in formulating a treatment pathway include comorbidity and fitness for surgery, liver and colorectal disease distribution and the optimal placement of chemotherapy in the care plan.

Given the treatment permutations to be understood, an inception cohort study is valuable to understand patient outcomes as a function of clinical decisions and patient/disease characteristics. The Colorectal cancer with Synchronous liver-limited Metastases: an Inception Cohort (CoSMIC) study will recruit patients with colorectal cancer with synchronous liver-limited hepatic metastatic disease, and aims to fulfil four objectives. First, the study will characterise the management of this cohort by reporting relationships between modes of presentation, management and adherence to or deviation from current clinical guidelines. The second objective of the CoSMIC study is to provide (for the first time) comparable outcome data on patients with colorectal cancer with liver-limited hepatic metastases treated by synchronous or sequential surgery. The third objective is to address (also for the first time in a structured, prospective fashion) the impact of treatment on quality of life using validated questionnaire methodology. Finally, in this typically complex care plan, it may be difficult for the patients’ voice to be heard and given due consideration. The focus on patient experience is important^23^ and may vary substantially according to the treatment pathway. Thus, as a fourth objective a parallel qualitative study of both patient and clinician experience will help inform the knowledge of current practice. Completion of the CoSMIC study protocol will provide important new evidence about the treatment of patients with colorectal cancer with synchronous liver-limited metastases and provide objective evidence to guide future studies (including randomised evaluations) in this area.

## Methods and analysis

### Aims of the study

The primary aims of the study are tocharacterise the management of patients with colorectal cancer and synchronous liver metastases, thus defining the relationship between presentation and treatment to demonstrate adherence to or deviation from an evidence-informed common pathway. It is accepted that modern management of this complex clinical scenario cannot be sufficiently addressed by a single pathway but the guidelines suggested by ESMO provide constrained management options: these include early use of neoadjuvant chemotherapy, surgical resection and adjuvant chemotherapy as the final stage. The treatment options within the common pathway standardise initial staging, accommodating treatment for liver metastases according to liver involvement and location of disease as well as different treatment requirements for patients with rectal primary cancer compared with those with colonic primary tumours;provide comparable and prospective outcome data on patients with colorectal cancer with liver-limited hepatic metastases treated by synchronous or sequential surgery;address the impact of treatment on quality of life using validated questionnaire methodology;understand and explore the patient and caregiver experience of their disease and their experiences through the treatment pathway, including their voice in treatment decision planning;understand and explore the clinician’s experience of providing care to patients, and their perspectives on treatment pathways, specifically in areas of clinical equipoise, that make treatment allocation difficult;explore the acceptability and barriers of a future randomised trial from both a clinician and patient’s perspective, with a focus on the ethical dilemmas and the potential clinical value of such a study.

### Design

An inception cohort study will evaluate the treatment and outcomes of patients with colorectal cancer with synchronous liver-limited hepatic metastases. A parallel phenomenological qualitative study will also explore the patient and caregiver experience of the disease and treatment, and separately, the clinician perspective of providing care.

### Setting

The study population will comprise patients with colorectal cancer with liver-limited hepatic metastases referred to the Hepatobiliary Surgical Unit at Manchester Royal Infirmary—an NHS regional cancer-network approved hepato-pancreato-biliary (HPB) centre with a formally constituted and National Cancer Network peer-review accredited MDT. The study opened for recruitment in April 2015 with prospective recruitment to be undertaken for 24 months.

### Participants

To be eligible for inclusion in this cohort study, patients must fulfil the following:

#### Inclusion criteria

Over18 years of ageAble to give informed consentHave a histological diagnosis of colorectal cancerNo prior history of malignancy.Have radiological evidence on either contrast-enhanced CT or contrast-enhanced MR scanning of hepatic metastases at the time of diagnosis of the primary tumour or within 3 months thereof. Liver metastases should not be biopsied.CT and/or fluorodeoxyglucose positron emission tomography ([^18^F]FDG-PET) evidence of the absence of extrahepatic metastasesMR scan assessment of local stage in those patients with rectal primary tumoursWHO performance status 0, 1 or 2 and considered by the MDT to be suitable for chemotherapyA subset of patients from the cohort will be selected by purposeful sampling for the qualitative study following completion of their treatment, and are able to take part in a structured interview

#### Exclusion criteria

Patients who are under 18 years of agePatients who are unable to give informed consentPatients who are unfit for the chemotherapy regimens in this protocolAny psychiatric or neurological condition assessed by clinical judgement to compromise the patient's ability to give informed consent or to comply with oral medicationPartial or complete bowel obstruction not amenable to resolution by stent or diversionPre-existing neuropathy (> grade 1)Patients with another previous or current malignant diseasePatients with known hypersensitivity reactions to any of the components of the study treatmentsPatients with distant metastases outwith the liverPatients who have received prior chemotherapy with oxaliplatinPatients with a personal or family history suggestive of dihydropyrimidine dehydrogenase (DPD) deficiency or with known DPD deficiencyFor patients selected for the qualitative study—those who are unable to give consent or are unfit to take part in a structured interview

For the clinician arm of the qualitative study, clinicians must fulfil the following:

#### Inclusion criteria

Consultant gradeIn clinical practice and an active participant of the HPB MDT in one of the following specialities: HPB surgery, colorectal surgery, radiology, oncology and histopathologyWilling to give informed consent

#### Exclusion criteria

Non-consultant gradeNot in clinical practice or an active participant of the HPB MDTUnwilling to give informed consent

### Recruitment

Patients will be formally identified prospectively at the weekly regional HPB MDT and approached in the outpatient clinic at MRI to discuss participation. Recruitment began in April 2015. For patients wishing to enrol, but where the treatment pathway has already started (typically those who presented with an acute abdomen secondary to the bowel lesion), data will be retrospectively collected on treatment already received. Missing data points, particularly quality of life prior to surgery, during data analysis will be compensated for by unit imputation.

Potential participants of qualitative study will be approached following completion of their treatment either in the outpatient clinic or by telephone to ascertain their interest in taking part in the interviews.

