#### Timelines for completion of the treatment protocol

For the purposes of this study, this is defined as the amount of time in days from enrolment to completion of the protocol. The term ‘protocol’ relates to completion of the common treatment pathway.

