#### Failure to complete the treatment protocol

This is defined as dropout prior to completion of the allocated treatment sequence. It will be further categorised as due to disease progression, patient choice or unrelated to colorectal cancer (for example myocardial infarction) and will be recorded as the time in days from enrolment.

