#### Mortality

Overall and cancer-related mortality in either arm after enrolment will be recorded. Mortality (and cause) will be determined using the Demographics Batch Service to access the national electronic database of the UK NHS.

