### Acknowledgement of selection bias

The liver metastases multidisciplinary team meeting at the Manchester Royal Infirmary is the sole forum approved by cancer commissioners for discussion of the care of patients with colorectal cancer liver metastases. The HPB unit guideline is that all patients with stage IV colorectal cancer should have their care reviewed at the MDT. However, it is acknowledged that there are several groups of patients who may bypass the MDT. In particular, patients with systemic disease ‘beyond liver’ may be referred for chemotherapy without consideration for liver surgery. From the patient’s perspective, this care pathway is appropriate. Similarly, patients who present to local MDTs with liver metastases who undergo bowel-first surgery but whose disease progresses rendering them unsuitable for consideration for liver surgery will likely not be referred. For the purposes of reporting the CoSMIC data, these sources of patient loss to study will be acknowledged together with any potential for selection bias. Reporting will be pragmatic and descriptive.

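### Patients who enrol after treatment has begun are timed from enrolment, which shortens bowel-first pathway times and hides early deaths

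*Protocol article*

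**What the plan says.** Recruitment: "Patients will be formally identified prospectively at the weekly regional HPB MDT and approached in the outpatient clinic at MRI to discuss participation". The same section also lets in patients "where the treatment pathway has already started (typically those who presented with an acute abdomen secondary to the bowel lesion"; for these, "data will be retrospectively collected on treatment already received".

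The clock is set outcome by outcome:
- Timelines for completion of the treatment protocol: "the amount of time in days from enrolment to completion of the protocol".
- Failure to complete the treatment protocol: this "will be recorded as the time in days from enrolment".
- Disease-free survival: the section heading places it 12 months after enrolment.
- Mortality: "Overall and cancer-related mortality in either arm after enrolment will be recorded".

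The Analysis plan groups patients as synchronous, liver first or bowel first, by the sequence they received. Acknowledgement of selection bias concedes that some patients who have bowel-first surgery through local teams, and "whose disease progresses rendering them unsuitable for consideration for liver surgery will likely not be referred", are lost to the study. It promises to acknowledge this and to report descriptively. Statistical methods adds exploratory regression and propensity score matching. The article sets no common time origin and no delayed-entry rule.

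**The concern.** An inception cohort should pick up every patient at the same point in the disease course. Here most are meant to be identified before surgery, but some enter after the first operation. The documents' own example of a late entrant is someone who presented with an acute abdomen from the bowel lesion, so late entry should fall mainly on one of the three compared sequences.

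For a late entrant, a clock that starts at enrolment leaves the completed stage out of pathway time. Entry also requires the patient to have survived and been referred, so earlier deaths and failures are invisible. Retrospective data collection recovers treatment details only for those who did enrol. The second aim of the study is comparable, prospective outcome data by sequence, and this bears directly on it. The article itself fixes the clock, so the point cannot be left to an analysis plan that is not shown.

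**Working it through.** **The plan's own figure.** Study size gives about 75 eligible patients a year for two years: 75 × 2 = 150. This reproduces and is unaffected. There is no power calculation to check, and the article gives no share of late entrants, no delay to enrolment and no event rates. All inputs below are therefore assumptions.

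**The passages side by side.** The section on failure to complete counts dropout through disease progression as a failure. The selection-bias section says bowel-first patients with that same event, before referral, will probably never enter. So progression is an outcome in a patient enrolled before surgery, but prevents entry in one who would have enrolled after it.

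**Pathway time.** Let f be the share of the enrolled bowel-first group that joined late, and L the days from first treatment to enrolment. Compared with a clock started at first treatment, mean pathway time is short by f × L.
- f = 0.25, L = 60: 15 days
- f = 0.50, L = 90: 45 days
- f = 0.75, L = 120: 90 days

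An assumed 300-day pathway would read 285, 255 and 210 days.

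**Early operative death and 12-month mortality.** Assume half of bowel-first starters begin before referral and 5% of all starters die early. Of late-route patients who survive that period, 20% are never referred. Enrolment is 3 months after the start for late entrants. Twelve-month mortality after the early period is 10% in referable and 40% in unreferred patients.
- Survival from treatment start: 0.5 × 0.95 × 0.90 + 0.5 × 0.95 × (0.80 × 0.90 + 0.20 × 0.60) = 0.4275 + 0.3990 = 0.8265, so mortality is 17.35%.
- Late entrants who reach enrolment: 0.5 × 0.95 × 0.80 × 0.90^(3/12) = 0.370.
- Survival as observed: (0.4275 + 0.370 × 0.90) / (0.5 + 0.370) = 0.874, so mortality is 12.6%.
- Early death as observed: (0.5 × 0.05) / 0.870 = 2.9%, against 5.0%.

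Setting non-referral to zero isolates the part the article does not disclose. Late entrants become 0.5 × 0.95 × 0.90^(3/12) = 0.463. Early death reads 0.025 / 0.963 = 2.6% against 5.0%, and 12-month mortality reads 12.3% against 14.5%.

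Across 25–75% starting before referral, 3–10% early death and 0–30% unreferred, observed 12-month mortality is about 0.6 to 12 points too low.

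**Counter-case.** Suppose instead no early deaths, no non-referral and a rising hazard: S(t) = exp[−(t/λ)^k], with 15% dead at 12 months from the start. Counting 12 months from enrolment at month 3 gives 1 − S(15)/S(3). For k = 2, (12/λ)² = −ln 0.85 = 0.1625 and (15² − 3²)/12² = 1.5, so mortality is 1 − exp(−1.5 × 0.1625) = 21.6%. For k = 1.3 it is 17.3%; for k = 1 it stays at 15%. Here the later clock makes mortality look worse.

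**The case against.** The article is candid. It names the loss of bowel-first patients who progress, calls its modelling exploratory, claims no powered comparison and states that the design is observational. Prospective identification is the rule and late entry the exception. The exclusion of prior oxaliplatin chemotherapy may limit how far along the pathway a late entrant can be. Clinical presentation is collected, so matching on it could drop patients without counterparts.

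Much of this stands, and it rules out several stronger readings.
- A reader might infer that the bowel-first group consists only of survivors who stayed referable. It does not: bowel-first patients discussed before surgery enrol prospectively.
- A reader might infer that bowel-first mortality must look too low and its disease-free rate too high. The documents do not fix that direction. Emergency presenters may have a worse prognosis, and the counter-case shows the sign can reverse.
- It is tempting to call 30-day mortality after the bowel operation zero by construction. That needs enrolment more than 30 days after surgery, and no interval is given. As printed, Box 1 lists 30-day mortality under liver resection, though the layout may be broken.
- One could say that, with 10, 20 or 30% of starters lost, an observed disease-free rate of 60% is really 54, 48 or 42%. Those inputs are assumed and applied to every bowel-first starter. If only half start before referral, a 20% loss gives 0.60 × (1 − 0.5 × 0.20) = 54%, a gap of 6 points rather than 12. The figure also measures mainly the non-referral already disclosed.

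The enrolment clock is not answered. The selection-bias section does not mention it, and neither regression nor matching can restore patients who never enrolled.

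**Conclusion.** The concern holds in a limited form. Late entry, a clock that starts at enrolment and grouping by sequence received together bias pathway time and early operative mortality in favour of bowel-first surgery. This acts through late entrants only. Its size depends on their share and delay: 15–90 days of pathway time over the ranges assumed, and early death of 5.0% reading as 2.6–2.9% when half of starters begin before referral. The latter also assumes that late entrants enrol after the early-death window. The groups are not comparable on later mortality or disease-free status either, but the direction there is open. Disclosing non-referral does not deal with the time origin.

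**What to change.** - Count pathway time and time-to-event outcomes from one origin in all three groups: the date of diagnosis of synchronous disease or of first treatment, taken from patient records. State which. Eligibility allows metastases to be found "at the time of diagnosis of the primary tumour or within 3 months thereof", so if diagnosis of synchronous disease is chosen, say how a bowel resection that preceded it is counted.
- For time-to-event outcomes, let late entrants join the risk set at enrolment (delayed entry).
- Flag late entrants, give their number and delay, and report them as a separate stratum.
- Leave their pre-enrolment operation out of between-sequence comparisons of early operative mortality.
- Add a sensitivity analysis restricted to patients enrolled before any resection. Making this the main comparison would be a trade-off, since it removes most emergency presenters.
- State that delayed entry does not correct non-referral driven by prognosis, so the existing caveat must stay.

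The cost is some added analysis, retrieval of dates that Box 1 does not list explicitly, and less precision for the bowel-first group in the restricted analysis. No new tests or visits are needed.
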